### Randomization and allocation concealment

Participants will be randomly categorized into TNRM-UN, TNRM-TA, or UN groups; the details of the allocation are as follows:

Randomization sequence generation (30): A statistician independent of the research team will generate the randomization sequence using Statistical Package for the Social Sciences (SPSS) version 25.0 (IBM Corp, USA) with a block randomization method. Sequences will be stratified by baseline CVS-FAS score and age to ensure balance between groups. The randomization list is password-protected and stored on a secure server accessed only by an independent statistician.

Allocation concealment protocol (31): Group assignments are sealed in sequentially numbered, opaque envelopes. Each envelope contains a folded card with the group assignment (TNRM-UN, TNRM-TA, or UN). The coordinator, uninvolved in recruitment or outcome assessment, opens envelopes in sequential order only after confirming participant eligibility. Envelopes are stored in a locked cabinet, and an external auditor will access logs weekly.

Preventive Measure of Bias: Participants and outcome assessors are blinded to group assignments. Acupuncturists could not be blinded due to procedural differences, but are instructed not to discuss treatment details. The statistician analyzing outcomes will receive anonymized datasets labeled “Group A/B/C,” and group identities are revealed only after final analysis.

### Blinding method

The participants will not be blinded due to the completely different therapies used in the three groups. Meanwhile, owing to the unique nature of acupuncture, it is unrealistic to turn a blind eye to acupuncture operators. However, manipulation, evaluation, and data analysis will be performed by independent Investigators. The evaluators and statisticians are blinded to the grouping information.

### Intervention

Each group will be divided into 33 participants who received TNRM-UN, TNRM-TA, and UN treatments separately for 6 weeks. The frequency of the intervention is 3 times per week, and the needles are left in place for 30 min.

### Three-needle of regulating the mind combined with the umbilical needle group

#### Regulating the mind therapy

##### Acupoint selection

Referring to previous studies (21, 32, 33), we chose Shenting (DU24), Baihui (DU20), and Naohu (DU-17) to regulate the mind, the locations of which are listed in Table 2. The acupoint positioning standard is referred to as the acupoint positioning standard (34).

**Table 2 T2:** Locations of acupuncture acupoints.

**Acupoints**	**Location**
Shenting (DU 24)	On the head, 0.5 cun directly above the midpoint of the anterior hairline.
Baihui (DU 20)	On the head, 5.0 cun directly above the midpoint of the anterior hairline, at the midpoint of the line connecting the apexes of both ears.
Naohu (DU-17)	On the head, 2.5 cun directly above the midpoint of the posterior hairline, in the depression on the upper border of the external occipital protuberance.
Fengchi (GB20)	In on the nape, below the occipital, on the level of fengfu (DU20), in the depression between the upper ends of the sternocleidomastoid and trapezius muscles.
Jiaji acupoints (EX-B2)	On each side of the back, below the spinous processes from the 1st thoracic vertebra to the fifth lumbar vertebra,0.5 cun lateral to the posterior midline, Select Jiaji acupoints (EX-B2)corresponding to the sixth cervical vertebra.
Pishu (BL20)	On the back, below the spinous process of the 11th thoracic vertebra.1.5 cun lateral to the posterior midline.

##### Procedures

Patients are asked to take the sitting position, and the skin of selected points is routinely sterilized. The used needles are disposable sterile needles with a length of 40 mm and a diameter of 0.25 mm and are produced in Suzhou Hwato Medical Instruments Co., Ltd., China. When acupuncture is applied to Shenting (DU24), the needle is penetrated horizontally for 25–30 mm into Baihui (DU20) so that the needle sensation is spread to the parietal and temporal regions. When acupuncture is applied to Baihui (DU20), the needle is inserted horizontally for 25 mm along the governor vessel so that the needle sensation is spread to the posterior top and temporal regions. When acupuncture is applied to Naohu (DU-17), the needle is inserted horizontally for 8–12 mm. Acupuncturists use the finger-cutting needle method and perform flat reinforcing and reducing maneuvers after producing sensations such as soreness, numbness, or swelling.

#### Umbilical needle therapy

##### Orientation selection

The positions of Kan, Zhen, Xun, Li, Kun, and Qian are selected according to the hologram of inner eight trigrams, outer eight trigrams, and “Luoshu” in the theory system of umbilical needling (35). Combined with our previous pilot study, acupuncture in these six positions is often effective. Locations of these positions and reference diagram are also summarized in Figure 2.

**Figure 2 F2:**
[figure not shown]
Locating table and schematic of selected umbilical needle orientations.

##### Procedures

After regulating the mind therapy, the patients are asked to slowly lie supine on the acupuncture massage bed with holes at the head of the bed, and the area of Naohu (DU-17) point is suspended to ensure the safety of acupuncture. The skin around the navel is routinely disinfected. With the umbilicus core as the center, the disposable sterile needles with a length of 25 mm and a diameter of 0.25 mm are horizontally inserted into the corresponding umbilicus wall for approximately 10 mm at Kan, Zhen, Xun, Li, Kun, and Qian positions in turn. The acupuncturists need to look for sensitive points with pressure and pain near the Kun, Li, Xun, and Qian positions, and when the tip of the needle is aimed at a sensitive point, the doctors use the twirling method to insert the skin, commonly known as a “shotgun.” After needling, the needle handles are adjusted such that they are connected to each other. The operation diagram of TNRM-UN therapy is summarized in Figure 3.

**Figure 3 F3:**
[figure not shown]
Schematic diagram of three-needle therapy for regulating the mind and umbilical needle therapy. ① Three-needle for regulating the mind; ② acupuncture massage bed with holes at the head of the bed; ③ umbilical needle therapy; ④ three-needle for regulating the mind and umbilical needle therapy.

### Three-needle of regulating the mind combined with traditional acupuncture group

#### Regulating the mind therapy

The method is the same as that for the TNRM-UN group, and the patients were asked to be in a prone position because of the need for traditional acupuncture treatment.

#### Traditional acupuncture therapy

##### Acupoint selection

The selected acupoints refer to *Acupuncture and Moxibustion Therapeutics*, (36) which is the recommended textbook for the National Higher Colleges of Traditional Chinese Medicine in the New Century. Primary acupoints involve bilateral Fengchi (GB20) acupoints, bilateral Jiaji (EX-B2) acupoints corresponding to the sixth cervical vertebra, and bilateral Pishu (BL20) acupoints. Locations of these acupoints are also summarized in Table 2.

##### Procedures

Patients are asked to select the prone position. After disinfecting the acupoint skin, the disposable sterile needles with a length of 40 mm and a diameter of 0.25 mm are inserted into the acupoint skin, causing patients to experience a sensation of soreness, numbness, or swelling. The needles are inserted about 15 mm toward the tip of the nose at bilateral Fengchi points. The Jiaji acupoints corresponding to the sixth cervical vertebra are inserted straightly for 12–20 mm. The acupuncture angle of Pishu points is 45° from the body surface, and the depth of the needle is about 20 mm.

##### Umbilical needle group

The method is the same as that used for the TNRM-UN group.

### Outcome measures

All outcome measurements will be assessed before treatment and after 6 weeks of treatment, and primary outcomes will also be assessed at 12, 24 weeks follow-up.

#### Primary outcome measures

(1) Cervical Vertigo Symptoms and Functional Assessment Scale (CVS-FAS) score (37): vertigo degree (8 points), vertigo frequency (4 points), vertigo duration (4 points), neck and shoulder pain degree (4 points), headache degree (2 points), daily life and work ability (4 points), and psychological and social adaptability (4 points).

(2) Qi and blood Deficiency Symptom Assessment Scale score (QBD-SAS) (38): tiredness degree (6 points), palpitations and shortness (6 points), complexion (3 points), tongue substance (3 points), and pulse pattern (3 points).

Lower scores on the above indicators indicate less severe symptoms. Prior to the analysis, the internal consistency of CVS-FAS and QBD-SAS will be evaluated using Cronbach's alpha (α > 0.7 required). Inter-rater reliability is confirmed via Cohen's κ (κ > 0.6) for dual evaluators.

#### Secondary outcome measures

Ultrasound Hemodynamic Assessment Protocol: Bilateral vertebral arteries Hemodynamic parameters including diameter value (DV), peak systolic velocity (PSV), end-diastolic velocity (EDV), pulsatility index (PI), and resistance index (RI) are measured using a Mindray Resona19S ultrasound system (Mindray, Shenzhen, China) with a linear array probe (L14-3WS, frequency: 5–12 MHz). The protocol adheres to international guidelines for vertebral artery assessment. Details of the measurements are standardized as follows:

(1) Patient positioning: Supine position with neck neutral alignment.

(2) Probe orientation: Longitudinal plane, parallel to the vertebral artery's anatomical course.

(3) Gain settings: Adjusted to minimize noise while maintaining vessel wall clarity (default: 60 dB).

(4) Sampling point: Mid-V2 segment (between C4–C6 transverse foramina), with a Doppler angle ≤ 60° and sample gate width 1.5 mm.

(5) Measurement protocol: Three consecutive measurements per side (total 6 per patient). Values from three cardiac cycles are averaged for each parameter (DV, PSV, EDV, PI, and RI). The average values of DV, PSV, and EDV are obtained by taking the arithmetic mean of all valid measurement values of the same parameter. The PI and RI values are calculated by the formulas PI = PSV – EDV/Mean velocity and RI = PSV – EDV/PSV, respectively; they are taken as the arithmetic mean of all valid measurements.

Ultrasound diagnostic criteria for CV (39): VD < 2.80 mm is defined as stenosis; Vmax < 35.00 cm/s, and Vmin < 15.00 cm/s are considered as decreased; RI > 0.70 and PI > 1.30 are considered as increased.

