### Clinical implications of hemodynamic changes

The hemodynamic parameters measured via color Doppler ultrasound–vertebral artery diameter (DV), peak systolic velocity (PSV), end-diastolic velocity (EDV), pulsatility index (PI), and resistance index (RI) are critical biomarkers for assessing vertebrobasilar insufficiency, a key contributor to cervical vertigo (CV). In clinical practice, increased arterial diameter (DV), peak systolic velocity (PSV), and end-diastolic velocity (EDV) reflect enhanced blood volume and velocity, which are associated with improved cerebral perfusion. Prior studies (39) have shown that PSV < 35 cm/s or EDV < 15 cm/s correlates with symptomatic dizziness, and VD < 2.80 mm is defined as vertebral artery stenosis. Normalization of these values post-intervention predicts reduced CV recurrence. Elevated RI (>0.70) and PI (>1.30) indicate heightened vascular resistance, often linked to arterial stiffness or stenosis. A reduction in these indices post-treatment suggests improved vascular compliance and downstream perfusion, which may alleviate symptoms such as nausea and lightheadedness (56). The clinical prognostic value of hemodynamics is as follows: Sustained hemodynamic improvements (e.g., stable PSV and reduced RI) are associated with long-term symptom remission and lower risk of cerebrovascular complications (57). For instance, patients with persistent PI > 1.30 have a 2.5-fold higher likelihood of recurrent vertigo (58).

In this trial, improvements in these parameters following TNRM-UN therapy may indicate restored vertebral artery flow dynamics, which aligns with symptom alleviation (e.g., reduced CVS-FAS scores). However, individual variability in hemodynamic-symptom correlation warrants cautious interpretation.

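### The PI and RI formulas lack parentheses: as printed they return values close to PSV and cannot be reconciled with the protocol's own cut-offs (minor)

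*Protocol article*

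**What the plan says.** PI and RI are two of the five vertebral artery parameters that make up the secondary outcomes. In Secondary outcome measures, item (5), the protocol article averages the direct measurements (diameter, PSV, EDV) and then defines the two indices by formula: "PI = PSV – EDV/Mean velocity and RI = PSV – EDV/PSV, respectively". The RI part, "RI = PSV – EDV/PSV, respectively", uses only the two velocities listed as outcomes; the PI part also needs a mean velocity. No other section gives these formulas in another form.

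The next paragraph of that section sets thresholds for the indices, "RI > 0.70 and PI > 1.30 are considered as increased", and for the velocities, "Vmax < 35.00 cm/s, and Vmin < 15.00 cm/s are considered as decreased". The Discussion section on clinical implications repeats the velocity limits under the names PSV and EDV ("PSV < 35 cm/s or EDV < 15 cm/s correlates with symptomatic dizziness").

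That Discussion section also fixes the direction of benefit. For PI and RI: "A reduction in these indices post-treatment suggests improved vascular compliance and downstream perfusion". For the velocities, higher values are read as better: increases in "peak systolic velocity (PSV), and end-diastolic velocity (EDV) reflect enhanced blood volume and velocity". One example it gives of lasting benefit is a PSV that stays put while RI falls.

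**The concern.** Division is done before subtraction, so the printed expressions take a pure number (EDV divided by mean velocity, or by PSV) away from a velocity in cm/s. The result is neither dimensionless nor on a scale where 0.70 or 1.30 means anything.

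The line matters because it is the operational definition of two outcome parameters and sits in a list meant to standardise the measurements. Data pass from paper CRFs to an electronic CRF. Anyone who derived the indices from recorded velocities, or checked device values against the protocol, would turn to this line. Followed to the letter, it would give two outcomes that are almost copies of PSV. When PSV rises, they would move opposite to the direction that the article calls improvement.

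**Working it through.** **Inputs.** From the article: the two printed formulas; PSV 35 and EDV 15 cm/s (its own velocity limits, used as a worked point); cut-offs RI 0.70 and PI 1.30. The article reports no PI or RI value, so there is no figure to reproduce. The test is whether each reading lands on the scale of the cut-offs.

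Mean velocity is not given. I assume it is EDV + w × (PSV – EDV) with w from 0.25 to 0.50, which is 20 to 25 cm/s at 35/15. RI does not depend on this.

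**Level at PSV 35, EDV 15 cm/s.**
- RI as printed: 35 – 15/35 = 35 – 0.429 = 34.57.
- RI with parentheses: (35 – 15)/35 = 20/35 = 0.571.
- PI as printed: 35 – 15/20 = 34.25 to 35 – 15/25 = 34.40.
- PI with parentheses: 20/20 = 1.00 to 20/25 = 0.80.

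**General bound.** If EDV ≤ mean velocity ≤ PSV, the subtracted ratio is at most 1, so each printed index lies within 1 unit of PSV. A grid over PSV 10 to 120 cm/s, with EDV from 1 cm/s to just below PSV, gave a largest gap of 0.998. The smallest printed values were 9.1 (RI) and 9.03 (PI). Printed RI therefore exceeds 0.70 for any PSV above 0.70 + 1 = 1.7 cm/s, and printed PI exceeds 1.30 for any PSV above 1.30 + 1 = 2.3 cm/s.

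**Direction.** The parenthesised RI equals 1 – EDV/PSV and the printed one equals PSV – EDV/PSV. They differ by PSV – 1, so:

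change in printed RI = change in parenthesised RI + change in PSV.

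The subtracted ratio can change by no more than 1, so a PSV rise of more than 1 cm/s always raises both printed indices. Illustrative changes (PI with w = 1/3 to 1/2):

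| Change (PSV; EDV, cm/s) | RI printed | RI with parentheses | PI printed | PI with parentheses |
|---|---|---|---|---|
| (a) 33 to 40; 9 to 16 | 32.73 to 39.60 (+6.87) | 0.727 to 0.600 (–0.127) | +6.86 | –0.29 to –0.41 |
| (b) 35 to 35; 10 to 15 | 34.71 to 34.57 (–0.143) | 0.714 to 0.571 (–0.143) | –0.15 to –0.16 | –0.31 to –0.44 |
| (c) 40 to 36; 10 to 14 | 39.75 to 35.61 (–4.14) | 0.750 to 0.611 (–0.139) | –4.16 | –0.32 to –0.47 |

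In (a), where both velocities rise, the printed indices go the wrong way. In (b) and (c), with PSV stable or falling and EDV rising, the two forms agree in sign. Pattern (b) is the one that the article itself cites as lasting benefit.

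**The case against.** The best defence is that this is a slip of notation and that the data will never see it. Several points support it:
- The same section says that all five parameters, PI and RI included, are measured on the ultrasound system. The formula sentence can be read as explaining what the indices are.
- PI needs mean velocity in either form, and mean velocity is not among the parameters in Table 1. This also suggests device output.
- Table 3 reports separate reliability figures. Intra-operator ICCs are 0.96 for PSV, 0.93 for PI and 0.95 for RI; inter-operator ICCs are 0.94, 0.89 and 0.90. If PSV differs between patients by several cm/s (an assumption), an index within 1 unit of PSV would have almost PSV's ICC. The reported values look more like distinct indices.
- The cut-offs beside the formulas make the intended meaning plain.

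All of this stands. It shows what was probably meant and probably done, but it does not make the printed line right. The section says both that the indices are measured and that they are calculated by formula, and does not settle which applies.

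Damaged typesetting is also possible: in the sample size formula the square appears as a detached (2). But that formula keeps its brackets, and the PI and RI expressions are plain inline text with a slash, so a lost stacked fraction is possible but unlikely.

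A reader might infer more: that every patient will be classed as increased, or that the haemodynamic results will come out with the wrong sign. The documents do not support either as a consequence for the trial. No analysis in the Statistical analysis plan section splits PI or RI at the cut-offs, the sign depends on what PSV does, and nothing shows that the printed expressions were applied.

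**Conclusion.** The formulas are wrong as written and conflict with the cut-offs in the same section. At 35/15 cm/s the printed RI is 34.57 against 0.571 with parentheses, and the printed PI is 34.25 to 34.40 against 0.80 to 1.00. The RI result needs no assumption; the PI range rests on the assumed mean velocity of 20 to 25 cm/s.

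Any harm is conditional. Only if the line were used to derive the outcomes would PI and RI largely repeat PSV and rise with it whenever it climbs by more than about 1 cm/s. The parenthesised indices are probably intended. The primary outcomes and the sample size are not touched. Severity: minor.

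**What to change.** Print PI = (PSV – EDV)/mean velocity and RI = (PSV – EDV)/PSV. State whether the analysed values are read from the device or calculated from recorded velocities. Use the same expressions in the CRF and the analysis code, with a range check that RI lies between 0 and 1.

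The cost is one line of text and one line of code. No new data are needed if the indices are device readings. If PI is to be calculated from recorded velocities, mean velocity must also be captured on the CRF.

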### Sample size estimation

PASS V.15.0 software (NCSS, Kaysville, UT, USA) is used for the sample size calculation, and eligible participants are separated into three groups in a 1:1:1 ratio. Owing to the lack of relevant randomized controlled trials (RCTs) and the exploratory nature of this clinical trial, we have to refer to a formula for estimating the sample size of multiple groups of randomized controlled trials: N = [(*Z*_α/2_ + *Z*_β_)σ/δ] (2) (${\text{Q}}_{1}^{-1}$ + ${\text{Q}}_{2}^{-1}$). Based on pre-experiment research data, after 20 patients received TNRM-UN treatment, the average reduction in CVS-FAS was 7.3 points, with a standard deviation of σ = 8.2; the standard deviation (σ = 8.2) in the formula is directly adopted from the pilot study to reflect population variability. Aligned with clinical consensus for vestibular disorders [Jacobson and Newman have supported using a 30%−50% reduction as clinically meaningful in vestibular outcomes in 1990 (40)], we conservatively set δ (δ = 5 points) as 60% of this observed effect. With α = 0.05, 1 – β = 0.9, and the sample number between groups Q1 = Q2 = 0.5, each group required 30 participants. Assuming a 10% dropout rate, 33 participants need to be included in each group; therefore, in total, we included 99 participants. To ensure robustness, we performed sensitivity analyses evaluating: When effect size (δ) variability was 4–6 points and standard deviation (σ) variability was 7.0 – 9.0, the results confirmed that the planned sample size (N = 99) maintained ≥80% statistical power across all plausible scenarios, supporting its adequacy even if assumptions deviated moderately from initial estimates.

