## Limitations

(1) The inherent inability to blind participants and acupuncturists in acupuncture trials introduces two key biases: (a) Performance Bias: Acupuncturists may unconsciously intensify treatment for the experimental group (TNRM-UN), inflating observed effects. (b) Reporting Bias: Participants aware of receiving active therapy may overreport symptom improvement, particularly for subjective outcomes. To this end, to mitigate bias partially, we will employ the following strategies:

(a) Standardized participant pre-treatment education: All participants will receive identical oral/written explanations about potential benefits of all interventions (TNRM-UN, TNRM-TA, and UN) to equalize expectations.

(b) Third-party outcome monitoring: Independent assessors will review video recordings of 30% randomly selected acupuncture sessions to ensure protocol adherence.

(c) We will incorporate an electronic health record (EHR) to track long-term outcomes, which can reduce subjective reporting reliance.

(2) Due to the lack of relevant RCTs, our sample size has to refer to the formula for the sample size of multiple groups of randomized controlled trials. The pilot trial's single-arm design (*n* = 20) may not fully capture variability in a three-group RCT. We conservatively set δ as 60% of this observed effect (δ = 5 points), while clinically justified, it lacks direct empirical validation for CVS-FAS, which requires empirical validation in future trials. Nevertheless, our study will provide compelling evidence for sample size estimation for future RCTs.

(3) Deficiency of qi and blood is the predominant TCM syndrome in CV (60%−70% in our hospital), and our study protocol may not apply to patients with other TCM syndromes. But we acknowledge the potential impact of subgroup proportion on generalizability. Future multisyndromic trials are needed to validate these results across broader populations.

(4) About ultrasonic measurements, while our measurement protocols align with the European Society of Neurosonology Guidelines for Extracranial Doppler Ultrasonography, subtle variations in sampling gate positioning or patient motion may affect PI/RI reproducibility. Future studies could employ automated angle-tracking software to minimize variability further.

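### δ = 5 is described as a conservative 60% of the pilot's 7.3-point change, but 60% is 4.38 and 5 is 68.5%; the pilot figure is also a single-arm change, not a between-arm difference

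*Protocol article*

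**What the plan says.** In the Protocol article, Sample size estimation, the planning inputs come from a pilot: "after 20 patients received TNRM-UN treatment, the average reduction in CVS-FAS was 7.3 points", with an SD of 8.2. The SD is carried straight into the formula: "the standard deviation (σ = 8.2) in the formula is directly adopted from the pilot study to reflect population variability". The planning difference is then fixed: "we conservatively set δ (δ = 5 points) as 60% of this observed effect". With two-sided α = 0.05, 90% power and Q1 = Q2 = 0.5, the section arrives at 30 per group, raised to 33 for 10% dropout.

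Limitations, item (2), makes the same claim: "We conservatively set δ as 60% of this observed effect (δ = 5 points), while clinically justified". That item refers to "The pilot trial's single-arm design" and concedes that δ has not been validated empirically for CVS-FAS.

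The Strengths section explains that TNRM-TA shares the three-needle component with TNRM-UN, and that UN shares the umbilical component. Both comparators are therefore active treatments that overlap with the experimental arm.

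**The concern.** Two things do not fit.

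- **The percentage is wrong.** The stated rule (60%), the stated base (7.3) and the stated result (5) cannot all be true. In a superiority calculation a larger δ gives a smaller N, so the mismatch runs against the claim of caution.
- **The base is a different quantity from δ.** The 7.3 is a before–after change in one treated group. Such a change includes natural course, regression to the mean and nonspecific response, and active comparators would share these. The formula needs the difference between two arms.

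δ drives the sample size and shapes how a null or positive result is read. A reader told that δ was set cautiously will take the trial to have a margin that its own figures do not show.

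**Working it through.** **Inputs (all from Sample size estimation):** pilot mean change 7.3; SD 8.2; pilot n = 20; δ = 5; stated fraction 60%; two-sided α = 0.05; power 90%; Q1 = Q2 = 0.5; 30 per group before dropout.

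**1. The percentage.**
- 0.60 × 7.3 = 4.38.
- 5 / 7.3 = 0.685, or 68.5%.
- 5 / 0.60 = 8.33. A δ of 5 is 60% only of an effect of 8.33, which the article does not report.

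**2. The plan's own figure.** The formula is N = [(Zα/2 + Zβ)σ/δ]² × (1/Q1 + 1/Q2), with Zα/2 + Zβ = 1.960 + 1.282 = 3.2415 (before rounding).
- δ = 5: (3.2415 × 8.2 / 5)² = 28.26. Multiplied by (2 + 2) this is 113.04 for two arms, or 56.5, so 57 per arm.
- The stated 30 per arm is not reproduced. That discrepancy exists at δ = 5 and has nothing to do with the 60% label.

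**3. What the mislabel alone changes.**
- δ = 4.38: (3.2415 × 8.2 / 4.38)² = 36.83. Multiplied by 4 this is 147.3, or 73.7, so 74 per arm.
- Ratio: (5 / 4.38)² = 1.30.

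**4. Power of one pairwise comparison at 30 per arm, σ = 8.2.** The noncentrality is δ / (8.2 × √(2/30)), which is 2.36 for δ = 5 and 2.07 for δ = 4.38.

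| Test | δ = 5 | δ = 4.38 |
|---|---|---|
| Two-sided t-test, α = 0.05 | 64% | 53% |
| Tukey's HSD, three groups | 49% | 38% |

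The Tukey row is given because Between-group comparisons names that test for the pairwise step. The sample-size section itself uses α = 0.05 without adjustment.

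**5. The base of the rule.**
- 95% CI for the pilot mean: 7.3 ± 2.093 × 8.2/√20 = 7.3 ± 3.84, or 3.5 to 11.1.
- If the TNRM-UN arm repeats 7.3 exactly, δ = 5 implies a comparator improvement of 7.3 − 5 = 2.3 points, and δ = 4.38 implies 2.92. The article reports no comparator change against which to judge either.

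**The case against.** **The error may lie in the label.** The article does not show how 5 was reached. It may have been chosen first and the percentage misreported afterwards. This stands: a reader might infer that 4.38 was rounded in the favourable direction, but the text does not show that, and ordinary rounding would give 4 or 4.4. What is certain is only that 5 exceeds what the stated rule yields.

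**δ may be a target difference.** The section links δ to clinical meaningfulness, and a target need not be an expected effect. That is fair, but the article derives the number as a fraction of the pilot effect and calls it conservative on that basis.

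**The true difference is unknown.** A reader might conclude that the real between-arm difference must be below 5. The documents do not support this, since no comparator response is given. The 2.3-point figure depends on TNRM-UN repeating 7.3, and the pilot interval is wide. Nor is there a basis for saying that a comparator shares half the regimen: the Strengths section says only that each shares one component.

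**It is partly disclosed.** The Limitations admit the single-arm pilot and the lack of validation, and the sensitivity range of 4–6 points contains 4.38. But the Limitations do not correct the percentage or say that 7.3 is not a between-arm difference, and they repeat the conservative label. The power of at least 80% claimed for the sensitivity range does not hold at δ = 4.38 and σ = 8.2: with all 33 per arm the t-test has 57%.

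**Most of the power shortfall has another cause.** This is correct. Power is already about 64% at δ = 5 with 30 per arm, because the formula does not give 30. Only the further fall to 53% belongs here.

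**Conclusion.** The point holds in a limited form. The derivation of δ is arithmetically wrong in both places: 5 is 68.5% of 7.3, not 60%. Relative to the protocol's own rule it is optimistic, and this needs no outside assumption.

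The second part is a gap in support, not proof of error. A within-arm change from 20 patients on one treatment cannot show that 5 points is a cautious difference against active comparators.

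The size attributable to the mislabel is 57 to 74 per arm, a factor of 1.30. In power terms it is about 11 percentage points at 30 per arm, under either the t-test or Tukey's HSD. These figures assume σ = 8.2, the article's formula for N, and equal arms. It would be wrong to attribute the whole distance from the stated 90% power to this point, because the mismatch between 30 and 57 per arm is a separate error and correcting δ alone would not repair it.

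**What to change.** Change Sample size estimation and Limitations (2) together, in one of two ways:

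- **Keep δ = 5.** State that it is about 68% of the pilot's within-arm change, and delete the word conservatively in both places. This costs a sentence in each section and a less favourable justification.
- **Apply the 60% rule.** Set δ to about 4.4 and restate the power at the planned size (about 53% for an unadjusted pairwise t-test at 30 per arm, about 38% under Tukey). This is more than a wording change, because the stated 90% power and the sensitivity claim of at least 80% would have to be revised as well.

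In either case, add one sentence saying that the pilot had no comparator and gives no between-arm difference. It can add that, if TNRM-UN repeats 7.3, δ = 5 implies a comparator improvement of 2.3 points. The formula's 57 per arm against the stated 30 should be corrected at the same time, as its own item.

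### The claim that 99 participants keep at least 80% power for every δ of 4–6 and σ of 7.0–9.0 is false: power runs from about 40% to 90%, and the base case itself is near 64%

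*Protocol article*

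**What the plan says.** The Sample size estimation section of the protocol article describes a 1:1:1 design ("eligible participants are separated into three groups in a 1:1:1 ratio") and a two-group formula for means that uses the two-sided normal quantile. Its inputs are:

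- σ: "the standard deviation (σ = 8.2) in the formula is directly adopted from the pilot study", where the pilot had 20 patients.
- δ: "we conservatively set δ (δ = 5 points) as 60% of this observed effect".
- Error rates: "With α = 0.05, 1 – β = 0.9".
- Group fractions Q1 = Q2 = 0.5.

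It arrives at 30 per group, raised to 33 for 10% dropout, 99 in total. It then turns to sensitivity analyses: "When effect size (δ) variability was 4–6 points and standard deviation (σ) variability was 7.0 – 9.0", and reports that "the results confirmed that the planned sample size (N = 99) maintained ≥80% statistical power across all plausible scenarios". It takes this as support for the sample's adequacy under moderate departures from the assumptions.

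Under Between-group comparisons, the parametric analysis is an unadjusted one-way ANOVA, followed by Tukey's HSD if the overall test is significant.

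**The concern.** The sensitivity statement is a numerical result, and everything needed to check it is in the same section. Over the stated ranges, the standardised difference δ/σ runs from 4/9 = 0.444 to 6/7 = 0.857, a near-doubling. A sample that just held 80% power at the low end would have power far above 90% at the high end. Thirty or so per arm is too few to hold 80% at a standardised difference of 0.444.

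The sentence matters because nothing else in the protocol shows what happens if the pilot's mean or SD is off. A reader who believed it would take a non-significant result as good evidence against a true difference of 4 to 6 points. At δ = 4 and σ = 9 with 30 evaluable per arm, the unadjusted comparison misses the difference about 60% of the time (100 − 39.5 = 60.5%).

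**Working it through.** **Inputs** (all from Sample size estimation): two-sided α = 0.05; base case δ = 5, σ = 8.2; ranges δ 4–6 and σ 7.0–9.0; 33 enrolled per arm; 10% dropout, hence about 30 evaluable. The comparison is pairwise, because the Discussion (Strengths of the study) frames the questions as the combined therapy against each control.

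**Step 1: the plan's own formula at the base case.** N = [(z for α/2 + z for β) × σ/δ]² × (1/Q1 + 1/Q2), with quantiles 1.960 + 1.282 = 3.242.

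- (3.242 × 8.2/5)² = 28.26.
- 28.26 × (2 + 2) = 113.04 for two groups together, so 57 per group.

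The stated 30 per group is not reproduced. The figure 28.26 before the two-group factor rounds up to 29, close to 30, which suggests the factor was dropped. That is an inference.

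**Step 2: power at the base case.** By the normal approximation, power ≈ Φ(δ/σ × √(n/2) − 1.96).

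- n = 30: (5/8.2) × √15 = 2.362; Φ(0.402) = 65.6%. With the noncentral t distribution, 64.1%.
- n = 33: (5/8.2) × √16.5 = 2.477; Φ(0.517) = 69.7%. With the noncentral t, 68.4%.

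The centre of the sensitivity range is already below 80%.

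**Step 3: the stated range.** Two-sample noncentral-t power, two-sided 5%. The Tukey columns use the studentized range for three groups with 87 and 96 degrees of freedom.

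| δ | σ | n = 30, unadjusted | n = 33, unadjusted | n = 30, Tukey | n = 33, Tukey |
|---|---|---|---|---|---|
| 4 | 7.0 | 58.6% | 62.8% | 43.6% | 47.9% |
| 4 | 8.2 | 45.9% | 49.7% | 31.5% | 34.9% |
| 4 | 9.0 | 39.5% | 42.8% | 25.9% | 28.7% |
| 5 | 7.0 | 77.6% | 81.5% | 64.9% | 69.8% |
| 5 | 8.2 | 64.1% | 68.4% | 49.4% | 54.0% |
| 5 | 9.0 | 56.2% | 60.4% | 41.2% | 45.4% |
| 6 | 7.0 | 90.4% | 92.9% | 82.3% | 86.2% |
| 6 | 8.2 | 79.6% | 83.3% | 67.3% | 72.2% |
| 6 | 9.0 | 71.9% | 76.0% | 58.0% | 62.9% |

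**Step 4: how much of the range reaches 80%.** Unadjusted 80% power needs δ/σ of at least 0.736 at n = 30 and 0.700 at n = 33. In the rectangle of area 2 × 2 = 4, the qualifying region is a triangle in the corner of large δ and small σ.

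- n = 30: δ from 5.15 at σ = 7, and σ up to 8.16 at δ = 6. Area ½ × 0.85 × 1.16 = 0.49, about 12%.
- n = 33: δ from 4.90 at σ = 7, and σ up to 8.57 at δ = 6. Area ½ × 1.10 × 1.57 = 0.86, about 22%.

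**Step 5: other readings, at the worst corner (δ = 4, σ = 9).**

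| Reading | Power |
|---|---|
| One-sided test, 30 / 33 per arm | 53.0% / 56.4% |
| ANOVA overall test, one arm differing, 30 / 33 per arm | 39.9% / 43.5% |
| Bonferroni at 0.05/3, 30 / 33 per arm | 25.1% / 27.8% |
| 33 against 66 pooled controls | 55.0% |
| 99 split over two arms | 59.9% |
| One-sample or paired formula, 30 / 33 | 68.2% / 72.3% |
| 99 in each arm (not the plan) | 87.8% |

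Only the last, which is not the design, meets the claim. Holding 80% at this corner needs 2 × [(1.960 + 0.842) × 9/4]² = 79.5, about 80 evaluable per arm.

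**The case against.** The strongest defences are these.

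- *The trial is called exploratory, and its limitations admit that a single-arm pilot of 20 may understate variability.* Both are true, but neither corrects a specific power figure, and the Discussion says the trial is meant to confirm superiority.
- *The sensitivity calculations are not shown and may have used another method.* They are not shown, but the inputs are, and none of the alternatives in step 5 holds 80% with the planned numbers. A one-sided test with all 33 per arm is kinder, yet about 45% of the range still falls below 80%, and the stated formula is two-sided.
- *Baseline adjustment could raise power.* The planned between-group test is unadjusted, and σ is quoted beside the pilot's mean reduction, so it appears to describe change scores already.
- *The claim concerns 99 participants, so 33 per arm is the fair figure.* This is reasonable, and both are shown. The conclusion is the same.
- *The Tukey figures go beyond a claim built on an unadjusted formula.* This stands in part. The claim fails without them, so the unadjusted figures should lead.
- *A σ range narrower than the pilot's confidence interval is a design choice.* This stands. With n = 20 and SD 8.2, the 95% interval for σ is 8.2 × √(19/32.85) = 6.2 to 8.2 × √(19/8.91) = 12.0. A range ending at 9.0 is narrow for something described as covering all plausible scenarios, but extending it is advisable, not a correction of an error.

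**Conclusion.** The concern holds and must be fixed. Pairwise power over the stated ranges is 39.5% to 90.4% with 30 evaluable per arm and 42.8% to 92.9% with 33. It is below 80% in roughly 88% and 78% of the range respectively, including the base case and every scenario with δ = 4. Those shares treat all points of the δ-by-σ rectangle alike.

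The power figures assume approximately normal outcomes with a common σ, a two-sided 5% level and no multiplicity adjustment. Allowing for Tukey only lowers them. The root cause is shared with the base calculation, where the formula gives 57 per group and not 30, so the two should be treated as linked errors.

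**What to change.** In Sample size estimation:

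1. Replace the sensitivity sentence with a power table for δ = 4, 5, 6 and σ = 7.0, 8.2, 9.0 at 30 and 33 per arm. Lead with the unadjusted figures and give the Tukey figures beside them, since that is the planned parametric comparison.
2. State the ranges plainly: about 40–90% unadjusted and 26–82% under Tukey at 30 per arm; about 43–93% and 29–86% at 33.
3. Delete the conclusion that the sample is adequate under moderate departures from the assumptions.
4. Correct the base calculation, or restate the design power as about 64% (30 per arm) or 68% (33 per arm). Otherwise the section would claim 90% and tabulate 64% for the same inputs.
5. Optionally, add a row at σ = 12.0, the upper limit of the pilot's confidence interval.

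The cost is a short table and a less favourable statement. The rewording changes nothing in the conduct of the trial, though honest figures may prompt the sponsor to reconsider the sample size. If 99 is kept, the report should present estimates with confidence intervals and should not read a null result as evidence against a 4–6 point difference.
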